### Study endpoints

2.6

The primary endpoint of this study will be the percentage reduction in the total number of days with DOACs from day 31 to day 360 compared to the conventional method of continuous anticoagulation. Analysis of the primary endpoint will be calculated as follows: the denominator will be the observation period (person‐days) and the numerator will be the total number of days with DOACs during the observation period. The degree of decrease will be evaluated by calculating “1 ‐ the rate of DOAC use during the observation period”. The observation period used in this calculation will be from day 31 to day 360. For DOACs taken twice a day, if taken only in the morning or evening, the days with DOACs will be counted as 0.5 days.

The secondary endpoints will include all‐cause death, stroke, systemic thromboembolism, bleeding events, and malfunctions of the Apple Watch. Bleeding events will be defined as major bleeding according to the ISTH bleeding criteria [10] and any overt bleeding events other than the major bleeding. Stroke will be defined as a non‐traumatic focal neurologic deficit lasting more than 24 hours, diagnosed by brain imaging or autopsy as ischemic stroke [11]. Systemic thromboembolism will be defined as a clinical history consistent with acute loss of peripheral blood flow and findings of embolism through objective testing such as imaging studies and surgical specimens.

### Research institutions: Osaka cardiovascular conference

2.7

The Osaka Cardiovascular Conference (OCVC) consists of the cardiologists affiliated with Osaka University Graduate School of Medicine and its associated hospitals. The OCVC was initiated in 2014 to address clinical questions in the realm of cardiovascular medicine. Among the 35 participating institutions, 9 hospitals that perform a large volume of invasive treatments for AF comprise the OCVC‐Arrhythmia investigators and will participate in this study.

### Sample size setting

2.8

The target sample size is 50 patients who remain free of AF for at least 30 days following the initiation of monitoring with the Apple Watch. This was determined based on the available resources, including time, personnel, and budget limitations.

### Statistical analysis

2.9

Patient background analysis will be performed on all patients, including those with AF within 30 days of the start of Apple watch monitoring. The primary and secondary endpoints will be analyzed in a population free of AF for at least 31 days after the start of monitoring by the Apple watch. All‐cause death, bleeding events, stroke, and systemic thromboembolism will be estimated by the Kaplan–Meier method. Those rates at 12 months and their 95% confidence intervals will be calculated using Greenwood's formula. Categorical variables were presented as counts (percentages) and compared using the chi‐squared test or Fisher's exact test, as appropriate. Continuous variables will be reported as mean (standard deviation) or median (interquartile range) and compared using the Student's t‐test, Mann–Whitney U test, or paired t‐test as appropriate. P‐values <0.05 will be considered statistically significant for superiority testing. Statistical analysis will be performed using R software (version 4.3.1 or higher; R Foundation for Statistical Computing).

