**Methods:**

This multicenter prospective single‐arm study will enroll patients who have maintained sinus rhythm post‐ablation and are on DOACs. The target enrollment is 50 patients free of AF for at least 30 days following the initiation of Apple Watch monitoring. If no AF occurs for the first 30 days of monitoring, anticoagulants will be discontinued on day 31. If AF is confirmed after day 31, DOAC administration will be resumed and continued until the end of the observation period. The primary endpoint is the reduction in the total number of days with DOACs from day 31 to day 360 compared to the conventional method of continuing anticoagulation. Secondary endpoints include all‐cause mortality, stroke, systemic thromboembolism, bleeding events, and Apple Watch malfunctions.

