**FIGURE 1 joa313194-fig-0001:**
[figure not shown]
Study design. The red line indicates continuation of DOACs, the blue line indicates discontinuation of DOACs, the solid line indicates continuation of monitoring by the Apple Watch, and the dashed line indicates the discontinuation of monitoring by the Apple Watch. Heartbeat notification is defined as high heart rate notification and irregular heartbeat notification. AF, atrial fibrillation; DOAC, direct oral anticoagulant; ECG, electrocardiogram.

If no AF occurs for the first 30 days of monitoring, anticoagulants will be discontinued on day 31. AF is defined as the notification of irregular heartbeats and a high heart rate indicated by the Apple Watch, and AF, atrial flutter, and atrial tachycardia indicated by 12‐lead ECG or Holter ECG.

If AF is detected on the Apple Watch by day 30, the patient will obtain an ECG with the Apple Watch. Monitoring with the Apple Watch will then be discontinued. Thereafter the patient will see a physician within 7 days, and the physician will evaluate the ECG obtained by the patient with the Apple Watch. If the physician determines that the patient is not in AF, monitoring with the Apple Watch will be resumed. If the physician confirms that the patient is in AF, DOAC administration will be continued until the end of observation period.

If AF is detected on the Apple Watch after day 31, the patient will obtain an ECG with the Apple Watch. Monitoring by the Apple Watch will then be discontinued. At the same time, DOAC administration will be resumed. Thereafter, the patient will see a physician within 7 days, and the physician will evaluate the ECG obtained by the patient with the Apple Watch. If the physician determines that the patient is not in AF, DOAC administration will be discontinued and monitoring by the Apple Watch will be resumed. If the physician confirms that the patient is in AF, DOAC administration will be continued until the end of observation period.

If AF is confirmed by various ECG tests without notification from the Apple Watch, such as voluntary ECG recording by the ECG application on the Apple Watch or ECG tests at hospitals, the subject will be examined by a physician and, if determined to be in AF, will continue or resume taking DOACs and terminate the monitoring via the Apple Watch.

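### Section 2.9 requires 31 AF-free days for the endpoint analyses while the rest of the article uses 30, so read literally the set is selected on the first day of the primary window

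*Protocol article*

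**What the plan says.** All references are to the protocol article.

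- **Analysis set (2.9 Statistical analysis).** The primary and secondary endpoints are analysed "in a population free of AF for at least 31 days after the start of monitoring".
- **Same section, one sentence earlier.** Baseline characteristics are described for everyone, "including those with AF within 30 days of the start of Apple watch monitoring". Run-in failure is thus set at 30 days.
- **Target (2.8 Sample size setting).** "The target sample size is 50 patients who remain free of AF for at least 30 days". The Methods paragraph of the abstract agrees: "The target enrollment is 50 patients free of AF for at least 30 days following the initiation of Apple Watch monitoring".
- **Design rule (2.2 Study design).** "If no AF occurs for the first 30 days of monitoring, anticoagulants will be discontinued on day 31".
- **Count (2.10 Study status).** 54 patients enrolled, four had AF in the first 30 days, and the other 50 are in guided therapy.
- **Primary window (2.6 Study endpoints).** The person-day calculation runs from day 31 to day 360.
- **AF pathway (2.2).** One rule opens "If AF is detected on the Apple Watch by day 30", the next "If AF is detected on the Apple Watch after day 31". Under both, AF confirmed by the physician means DOACs to the end of observation.

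**The concern.** A 30-day AF-free requirement is an ordinary run-in criterion: it is settled before DOACs are stopped and before the outcome window opens. A 31-day requirement is different, because day 31 belongs to the period in which the strategy is being judged. A patient with AF on that day has already entered guided therapy, yet the wording of 2.9 puts that patient outside the endpoint population.

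AF is not itself the primary endpoint, but confirmed AF determines it, because DOAC days then accrue to the end of observation. A patient excluded for confirmed AF on day 31 would therefore have close to the worst possible primary outcome. The same set governs the secondary endpoints, so any stroke, bleed or death in that patient would also drop out of the safety results.

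The two consecutive sentences of 2.9 do not fit together either: a patient with first AF on day 31 is neither a run-in failure under the first nor in the endpoint set under the second.

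**Working it through.** **1. The article's own count.** Under the 30-day rule, 54 − 4 = 50. This reproduces the 50 patients in section 2.10 and the target in section 2.8, so the reported number rests on 30 days, not 31.

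**2. The window (2.6).** 360 − 31 + 1 = 330 days. With full follow-up, 50 × 330 = 16,500 person-days. With one patient removed, 49 × 330 = 16,170.

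**3. Shift from one excluded patient with confirmed AF.** Assume that this patient takes DOACs on all 330 days (reduction 0) and that the other 49 have a pooled reduction R.

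- Patient included: R × 49/50.
- Patient excluded: R.
- Difference: R − R × 49/50 = R/50.

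For R, I use the range the Introduction quotes from earlier device-guided studies, as an illustration only.

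| R in the other 49 | Included | Excluded | Shift (points) |
|---|---|---|---|
| 74.6% | 73.1% | 74.6% | +1.5 |
| 94% | 92.1% | 94.0% | +1.9 |
| 100% (limit) | 98.0% | 100% | +2.0 |

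**4. How likely such a patient is.** The article does not say whether anyone had AF on day 31. Assume that the run-in rate carries over.

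- Daily hazard: −ln(1 − 4/54)/30 = 0.00257.
- Probability of AF on day 31: 1 − exp(−0.00257) = 0.00256.
- Expected number among 50: 50 × 0.00256 = 0.13.
- Chance of at least one: 1 − (1 − 0.00256)^50 = 12%.
- Expected bias: 0.13 × 1.5 = 0.19 to 0.13 × 1.9 = 0.24, that is, about 0.2 points.

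At a quarter of that rate, the expected number is 0.03 and the chance of at least one is 3%.

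**5. A day-31 notification that is not confirmed.** If a notification alone counted as AF for the analysis set, a patient with a false alarm on day 31 would also be excluded. Section 2.2 has DOACs resumed until a physician review within 7 days. Taking 7 days, use is 7/330 = 2.1%, a reduction of 97.9%. Removing this patient changes the estimate by (R − 0.979)/50: −0.5 points at R = 74.6% and −0.1 points at R = 94%. The shift is downward.

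**6. The pathway wording.** The two watch-detection rules in 2.2 cover days up to 30 and days after 31. Taken literally, a watch detection on day 31 falls under neither. The last paragraph of 2.2 covers AF found by ECG without a watch notification and has no day limit, so the gap is confined to watch-detected AF.

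**The case against.** The strongest reply is that 31 is a slip for 30, or shorthand for still being AF-free when day 31 arrives. The sentence before it, the count in 2.10 and the stopping day all point that way. This is plausible, and it argues against reading the sentence as a deliberate choice. But it is the only sentence in the article that defines the endpoint population, and as written it gives a different set from the target and the count.

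Day numbering is a related defence. The article does not say whether monitoring starts on day 0 or day 1. If it starts on day 0, 31 days would end on day 30, before the window. The 30-day statements would then end on day 29, so the mismatch would remain. Following the first 30 days with a stop on day 31 fits a day-1 start better.

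Four stronger readings are tempting, and the article does not support them:

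- **That a patient has been dropped because of the outcome.** No such patient, and no intention to drop one, appears.
- **That the bias is about 2 points and always favourable.** Two points is the ceiling per confirmed case, reached only if every other patient takes no DOAC. The favourable direction holds only for physician-confirmed AF (working, step 5).
- **That falling below 50 would cost power or precision.** Section 2.8 bases 50 on time, personnel and budget, so no stated power or precision target is lost at 49.
- **That AF on day 31 has no rule at all.** Only watch-detected AF is left open, and the phrase about the period after day 31 may be meant to include day 31.

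**Conclusion.** The inconsistency is real and section 2.9 is wrong as written. It conflicts with every other definition of the population in the article and, with monitoring counted from day 1, makes entry to the analysis set depend on an event on the first day of the primary window.

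The likely numerical effect is small. Each excluded patient with physician-confirmed AF raises the estimated reduction by 1.5 to 1.9 points over the illustrative range, and by 2.0 at most, assuming full follow-up and DOAC use throughout the window. The expected bias of about 0.2 points rests on the assumption that the run-in AF rate continues to day 31; it is smaller if the rate falls. The case for correction is that an analysis set should not depend on events after the strategy has started, and that the repair is simple.

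**What to change.** **Section 2.9.** Define the population for the primary and secondary endpoints as patients free of AF for the first 30 days of monitoring (days 1 to 30), in line with section 2.8. AF from day 31 onward then counts in the endpoints, and the analysis set matches the 50 patients in section 2.10. State that the first day of monitoring is day 1.

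**Section 2.2.** The two watch-detection rules leave day 31 unassigned and must be reconciled with each other and with the day-31 stopping rule. This is clinical management, so the choice of rule is left to the investigators.

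**Cost.** These are wording changes, with no new data and no change in sample size. Enrolment is complete and the protocol is board-approved, so if the full protocol carries the same text, a formal amendment may be needed. The change to 2.9 should be made before the endpoint analysis.

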### Data collection and follow‐up

2.5

At the time of informed consent, baseline data, medical history, comorbidities, medications, blood test, 12‐lead ECG, transthoracic echocardiogram, date of catheter ablation for AF, and type of AF prior to ablation will be collected. After the enrollment, patients will continue to wear the Apple Watch until the end of the observation period, 12 months after enrollment. Patients will be strongly encouraged to wear the Apple Watch even while sleeping.

Patients will be followed at 1, 3, 6, 9, and 12 months after enrolment. A 12‐lead ECG, alerts, and ECG of the Apple Watch, number of days wearing the Apple Watch, and DOAC medication status will be obtained at each follow‐up visit. Medication assessment will be performed at 12 months. Symptom‐driven 12‐lead ECG, Holter ECG, and any other devices capable of obtaining ECGs can be used at any time at the physician's discretion. Outcomes, adverse events, and malfunctions of the Apple Watch will be collected whenever they occur during the observation period.

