### Study status

2.10

Between July 2023 and April 2024, a total of 54 patients were enrolled from the 9 sites. The target sample size (*N* = 50) was achieved in April 2024 **(Figure**
**2**
**)**. Four patients experienced AF during the first 30 days, and remaining 50 patients are undergoing the Apple watch‐guided antithrombotic therapy. Follow‐up of the last enrolled patient will be completed in April 2025 and primary results are expected to be available in late 2025.

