## DISCUSSION

3

This Up to AF trial is designed to investigate whether Apple Watch‐guided personalized anticoagulation therapy—where DOACs are continued or discontinued depending on the presence or absence of AF monitored by the Apple Watch—will reduce the use of DOACs compared to the conventional method of continuous anticoagulation.

After catheter ablation for AF, the risk of bleeding and embolization with oral anticoagulation is 1.0 to 1.6% and 0.2 to 1.0% per year, respectively, while the risk of bleeding and embolization without oral anticoagulation is 0.02 to 0.8% and 0.03 to 0.6% per year, respectively [6, 12, 13]. Meta‐analyses have found that discontinuing anticoagulation reduces bleeding risk but does not change embolic risk [14, 15]. Of note, our study evaluates a safer and more effective treatment strategy than the previous blind therapy. Since no evidence of such strategy exists to date, and a large‐scale trial would be required to evaluate clinical outcomes of the strategy, we conducted the current pilot study with a surrogate of anticoagulant use.

The ASSERT study found that subclinical AF shorter than 24 hours in duration had no different embolic events than no subclinical AF, while subclinical AF longer than 24 hours in duration had significantly more embolic events compared to no subclinical AF [17]. The NOAH‐AFNET 6 study showed that in a population with a median atrial high‐rate episode duration of 2.8 hours, anticoagulation does not reduce embolic events and only promotes bleeding events [18]. Patients with low AF burden are thought to be at low risk of embolic events according to these studies. A study with continuous cardiac rhythm monitoring showed >98% AF burden reduction by catheter ablation [19]. Nevertheless, since there have been reports that embolic events were more frequent with CHA_2_DS_2_‐VASc score of 4 or higher [16], the selection criterion for this study was set to CHA_2_DS_2_‐VASc score 3 or lower for safety reasons.

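### The Greenwood confidence intervals fixed for the safety endpoints fail when no event occurs, which is the likely result for stroke and systemic thromboembolism in 50 patients

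*Protocol article*

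**What the plan says.** Section 2.9 (Statistical analysis) lists all-cause death together with three other outcomes: "bleeding events, stroke, and systemic thromboembolism will be estimated by the" Kaplan–Meier method. It continues: "Those rates at 12 months and their 95% confidence intervals will be calculated using" Greenwood's formula. It names no interval scale (plain, log or log-log) and no alternative for endpoints with few or no events. The software is R.

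The group is small. Section 2.8 states: "The target sample size is 50 patients who remain free of AF for at least 30 days", and gives the basis: "This was determined based on the available resources, including time, personnel, and budget limitations". Section 2.10 confirms the number: "Four patients experienced AF during the first 30 days, and remaining 50 patients are undergoing the Apple watch". Section 2.5 has the watch worn "until the end of the observation period, 12 months after enrollment".

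The Discussion supplies the event rates. Off treatment, "the risk of bleeding and embolization without oral anticoagulation is 0.02 to 0.8% and 0.03 to 0.6% per year, respectively". On treatment, "the risk of bleeding and embolization with oral anticoagulation is 1.0 to 1.6% and 0.2 to 1.0% per year, respectively".

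**The concern.** Greenwood's variance is a sum over the times at which events occur. With no event there is nothing to sum, so the standard error is zero however few patients were followed. The resulting interval has no width, or cannot be computed at all.

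The introduction says that the trial will investigate the efficacy and safety of watch-guided anticoagulation, and the Discussion says that no evidence on such a strategy exists yet. The embolic endpoints carry the main safety question when DOACs are stopped. A line reading 0% (95% CI 0% to 0%) for stroke would suggest that the risk is known exactly, when 50 patients leave it wide open.

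**Working it through.** The article states no precision or event calculation, so there is no figure of its own to reproduce.

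**Inputs**
- n = 50 (sections 2.8 and 2.10).
- Follow-up T = 1 year (section 2.5). As a check, T = 330/365.25 = 0.903 year, for days 31 to 360.
- Yearly rates r from the Discussion: embolism 0.03–0.6% off and 0.2–1.0% on anticoagulation; bleeding 0.02–0.8% off and 1.0–1.6% on.
- Complete follow-up is assumed unless stated otherwise.

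**Step 1: the interval with no event.** Var(S) = S² × Σ d/[n(n − d)]. With no event S = 1 and the sum is 0, so SE = 0. R's survfit, run on 50 event-free patients, returned survival limits of 1 to 1 on the log (default) and plain scales, that is, an event rate of 0% to 0%. On the log-log scale it returned NA.

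**Step 2: how likely no event is.** P(0) = exp(−50 × r × T).

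| Endpoint and rates | Expected events, T = 1 | P(0), T = 1 | P(0), T = 0.903 |
|---|---|---|---|
| Embolism, off: 0.03% to 0.6% | 0.015 to 0.30 | 98.5% to 74% | 98.6% to 76% |
| Embolism, on: 0.2% to 1.0% | 0.10 to 0.50 | 90% to 61% | 91% to 64% |
| Bleeding, off: 0.02% to 0.8% | 0.01 to 0.40 | 99% to 67% | 99% to 70% |
| Bleeding, on: 1.0% to 1.6% | 0.50 to 0.80 | 61% to 45% | 64% to 49% |

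The rows marked on are bounding cases, with all 50 patients on a DOAC throughout. No event is the likelier result at any yearly rate below −ln(0.5)/50 = 1.39%. Every embolic rate quoted lies below this.

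**Step 3: what it does to coverage.** On the plain and log scales the interval 0% to 0% excludes every non-zero risk. At a true risk of 0.6% it therefore misses the truth in at least 74% of trials, so coverage is at most about 26%. At 0.03% coverage is at most about 1.5%.

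**Step 4: a valid interval with no event.** The Clopper–Pearson upper limit is 1 − 0.025^(1/n).
- 0/50: 1 − 0.025^(1/50) = 7.1%. Then 7.1/0.6 ≈ 12, and 7.1/1.0 ≈ 7.
- If only 45 or 40 patients reach 12 months (assumed numbers): 7.9% or 8.8%.

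**Step 5: one event, no censoring.** S = 0.98 and the Greenwood sum is 1/(50 × 49), so SE = 0.98 × √(1/2450) = 0.0198.

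| Interval for 1/50 | Lower | Upper |
|---|---|---|
| Greenwood, plain: 2% ± 1.96 × 1.98% | −1.9% | 5.9% |
| Greenwood, log (before truncation) | −2.0% | 5.8% |
| Greenwood, log-log | 0.3% | 13.4% |
| Exact | 0.05% | 10.6% |

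The plain and log intervals are too short at the top. The log-log interval is not.

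**The case against.** A good deal can be said on the other side, and part of it stands.

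- **Scope.** A reader might infer that all four safety endpoints will probably show no event. The article does not support that. It gives no mortality rate. Its bleeding endpoint (section 2.6) counts any overt bleed as well as ISTH major bleeding, so the quoted bleeding rates may be too low for it. Patients with confirmed AF stay on a DOAC, and with all 50 at the top on-treatment bleeding rate P(0) falls to 45%. The probabilities also apply to each endpoint singly: at the upper off-treatment rates, the chance of neither an embolism nor a bleed is exp(−50 × 0.014), about 50%. This stands, and it confines the claim of likelihood to stroke and systemic thromboembolism.
- **Scale.** Greenwood's formula gives a variance, and the interval scale is a separate choice that an analysis plan may make. A reader might infer that Greenwood limits are always too low with one event. They are not, because the log-log upper limit exceeds the exact one. With no event, however, no scale helps: the interval is either of zero width or undefined.
- **Comparison.** A reader might take 0.6% as the highest embolic rate in the article. It is the highest off anticoagulation; on anticoagulation the article quotes up to 1.0%. Both ratios are therefore given.
- **Weight.** These are secondary endpoints. The Discussion calls the trial a pilot with a surrogate outcome and says that clinical outcomes need a large trial. No stopping rule or decision in the article depends on these intervals. That is fair, and it lowers the priority.
- **Left to the analysis plan.** A fallback for zero events might be given there. If so, the point is closed. But the article does not leave the method open: it names Greenwood's formula, and a plan that follows it inherits the fault.

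**Conclusion.** The point holds as a recommended correction to the reporting of secondary endpoints. The stated method gives no usable interval when no event occurs. For stroke and systemic thromboembolism that outcome has a probability of about 74% to 98.5% at the quoted off-anticoagulation rates, and 61% to 90% at the on-anticoagulation rates. For bleeding it is possible but less certain, and for death it cannot be judged from the article. With one event the plain and log intervals are also poor.

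The probabilities assume that the Discussion's embolic rates apply to these patients and cover stroke and systemic thromboembolism together. If so, no event is at least as likely for each endpoint taken alone. The 7.1% bound assumes that all 50 patients complete 12 months.

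Two stronger readings are not supported. The article does not claim that an absence of events would prove safety; the risk is that a printed 0% to 0% would be read so. The fault also does not reach the primary endpoint, which is a proportion of days on DOACs. Exact intervals would display how little 50 patients can exclude, but would not change it.

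**What to change.** In section 2.9, replace the Greenwood intervals for death, bleeding, stroke and systemic thromboembolism with intervals that are valid for zero or few events. Use Clopper–Pearson limits on patients if 12-month follow-up is complete. Otherwise use exact Poisson limits on person-years or the beta product confidence procedure. The Kaplan–Meier point estimates can stay.

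Add that the safety conclusion will go no further than the resulting upper limit: 7.1% for 0/50 with complete follow-up, and higher with losses (for example 7.9% for 0/45, an assumed number).

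The cost is a sentence or two in the analysis section, with no new patients or data. The downside is that the reported safety intervals become wider and look less favourable. The choice should be recorded before the results are analysed; section 2.10 places the end of follow-up in April 2025 and primary results in late 2025.
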